## Discussion

8

MetS is a common chronic condition among elderly individuals, characterized by disorders in glucose and lipid metabolism, with chronic inflammation as core pathological features. Although omega-3 PUFA effectively regulate lipid metabolism and suppress inflammation, compliance with traditional omega-3 supplementation methods remains generally low among Chinese populations due to insufficient dietary intake. Omega-3 PUFA-enriched eggs provide a convenient dietary intervention approach; however, their effects on elderly individuals with MetS require further investigation. This study design a three-arm, parallel-group randomized controlled trial to evaluate the effects of omega-3 PUFA-enriched eggs on metabolic phenotypes in elderly patients with MetS in a real-world community setting. A 12-week intervention with multiple follow-up assessments will be conducted to systematically explore the practical application and efficacy of omega-3 PUFA-enriched eggs in this population.

This study will incorporate three intervention groups (omega-3 PUFA-enriched eggs, regular eggs, and blank control group) to establish a robust multi-level comparative framework. The comparison between the omega-3 PUFA-enriched eggs group and the regular eggs group will specifically isolate the incremental effect of omega-3 enrichment. The regular eggs and blank control groups will provide references to quantify the basic effects of egg consumption. Direct comparisons between the omega-3 PUFA-enriched eggs and blank control groups will be helpful for revealing the integrated intervention effects. Repeated measurements and biological sampling will be conducted at Weeks 0, 4, 8, and 12, balancing endpoint assessment with dynamic tracking of intervention effects and providing crucial temporal insights into the association between compliance and efficacy. This approach will overcome the limitations of single-endpoint evaluations in capturing intervention dynamics. In addition to standard clinical outcomes, this study will include analyses of multiple biological samples (blood, urine, stool), as well as evaluations of gut microbiota and metabolomics, enabling comprehensive exploration of the underlying biological mechanisms alongside efficacy assessments.

The primary challenges of this study will be compliance management and bias control. To enhance the implementation of the intervention, semi-structured interviews focusing on compliance barriers, intervention feasibility, and facilitating factors will be incorporated during the design phase to ensure alignment between the intervention format and the daily habits of elderly participants. Insights gained from these interviews will improve the feasibility of the intervention and participant compliance by optimizing trial procedures. This integration of qualitative methods will not only facilitate the smooth implementation of the trial but also provide practical guidance for future community-based applications. At the intervention level, rigorous compliance management will be achieved by first establishing trust with participants through clear explanations of the study objectives and significance. Efficient communication channels will be maintained via telephone, WeChat, SMS, and home visits. During the intervention period, follow-up will be conducted using a strategy of “daily participant diary + daily online review by investigators + weekly offline egg distribution and diary collection”.

Regarding data quality control, all researchers will receive standardized training on trial procedures, questionnaire administration, and technical operations. Questionnaires will be collected and reviewed on-site during follow-up visits. Dietary records will be carefully verified, and a double data-entry system with cross-verification will be implemented to ensure high data integrity. Anthropometric measurements—including height, weight, waist circumference, and blood pressure—will be taken twice to enhance accuracy. Food photo models will be used to guide participants in completing dietary frequency questionnaires, thereby improving the accuracy of intake estimation. Participants will receive clear instructions and training on questionnaire completion. Data from participants who no longer meet the study criteria will be excluded, and the reasons for withdrawal will be documented in detail.

For bias control, randomization sequences will be generated by independent statisticians, and allocation concealment will be ensured using opaque envelopes. Group assignment will be performed by non-enrolling investigators to minimize investigator bias. Regarding blinding, this trial will adopt an “open-label control with blinded intervention arms” design. The two types of eggs (omega-3 enriched vs. regular) will be identical in appearance and differentiated only by coded labels. Although participant blinding will not be feasible in the blank control group, the limitations of blinding will manifest in the following aspects. First, the open-label status of the blank control group will make participants explicitly aware that they are receiving no intervention, potentially inducing negative expectation effects and feelings of deprivation, which may lead to deterioration in health behaviors or reporting bias in symptom assessment. Although participants in the two blinded egg groups will be unaware of the specific egg type they receive, being informed of “receiving an egg intervention” may still generate positive expectations. The gradient distribution of expectation intensity across the three groups (hypothesized as: blank control < regular eggs < omega-3 PUFA-enriched eggs) will create an imbalance in expectation effects, making it impossible to distinguish whether between-group differences originate from the intervention itself or from differential psychological expectations. Second, participants in the control groups may voluntarily modify their dietary behaviors (e.g., increasing egg consumption) to compensate for the sense of deprivation, resulting in inter-group contamination and dilution of intervention effects. Third, despite the blinding of intervention administrators, outcome assessors, and data analysts, subjective outcome measures will remain susceptible to participant expectations; while objective biochemical indicators, although relatively robust, could still be confounded by behavioral changes in the control groups. Furthermore, divergent expectation levels among the three groups may lead to heterogeneous variance in outcome variables, and the potentially higher attrition rate in the blank control group could cause non-random missing data, threatening the validity of statistical inference. These limitations will exert multidimensional impacts on internal validity. First, expectation effects cannot be excluded as a confounding factor, meaning that the observed effects of omega-3 PUFA-enriched eggs may represent a combination of true biological effects, placebo effects, and negative expectation effects from the control group, with the weighting of each component remaining indeterminate. Second, it will limit the generalizability of the results to scenarios with uniform blinding or open-label conditions. In conclusion, the open-label status of the control group will constitute a source of systematic bias. Causal language should be used cautiously when interpreting results; priority should be given to objective biochemical indicators, and sensitivity analyses alongside process evaluations will be conducted to quantify the extent of bias. Nevertheless, allocation concealment, third-party randomization, assessor blinding, and post-data-lock unblinding will also be implemented to partially attenuate these biases.

Several other limitations should be acknowledged. First, complete participant blinding will not be achievable due to the absence of egg distribution in the blank control group, which may introduce expectation or behavioral bias. Second, dietary intake and compliance will be partly self-reported, potentially leading to recall or social desirability bias. Such bias will be minimized through strict quality control, double data entry, and validation using objective indicators. Third, the 12-week intervention period in this study will be sufficient to evaluate the acute effects of omega-3 PUFA-enriched eggs on blood lipids, gut microbiota, and metabolomic profiles; however, considering the ecological resilience of gut microbiota, longer intervention durations or post-intervention follow-up will be beneficial for assessing the sustainability of these changes. Future research will explore 6-month intervention designs with washout periods to verify the stability of gut microbiota alterations. Finally, variability in cooking methods and dietary substitution may influence individual exposure levels and metabolic outcomes. Although boiled eggs will be provided to participants living near community hospitals, cooking practices cannot be fully controlled in elderly individuals with limited mobility. Therefore, dietary surveys and follow-up records will be incorporated for covariate adjustment and sensitivity analyses, enhancing the robustness of result interpretation.

Regarding the innovation of this study, the research focuses on eggs as a delivery vehicle for omega-3 fatty acids. While existing omega-3 intervention studies have primarily relied on fish oil or algal oil capsule supplements— which have demonstrated benefits for gut microbiota and metabolic health—elderly populations face significant implementation barriers, including dysphagia, gastrointestinal intolerance, and poor long-term adherence. This study will employ omega-3 PUFA-enriched eggs as a daily food-based delivery vehicle, which combines high bioavailability with dietary accessibility, providing a sustainable and scalable alternative for elderly adults with metabolic syndrome. Research on this specific delivery vehicle remains limited. Regarding the target population, this study will focus on elderly adults with metabolic syndrome. Although the multi-omics mechanisms of omega-3 PUFAs in metabolic health have been extensively explored, integrated intervention studies specifically targeting elderly MetS patients remain scarce. Elderly adults exhibit unique metabolic characteristics (sarcopenia, insulin resistance, decreased gut microbiota diversity) and intervention sensitivity; this study will address the evidence gap for food-based omega-3 PUFA-enriched egg interventions in this specific subpopulation. Methodologically, this study will integrate plasma omega-3 exposure biomarkers, clinical metabolic phenotypes, and multi-omics endpoints to establish a longitudinal “exposure-microbiota-metabolite-phenotype” association network. Distinguishing from traditional designs that analyze clinical or omics endpoints in isolation, this study will employ mixed-model repeated measures analysis to reveal dynamic response patterns, providing an integrative perspective for understanding the systemic mechanisms of omega-3 PUFA-enriched eggs on health outcomes. Additionally, this study will concurrently assess adherence and acceptability during the 12-week intervention, documenting the dose-response relationship between actual egg consumption and plasma omega-3 responses, thereby providing implementation science evidence for the development of community-based nutritional intervention strategies for elderly adults.

In conclusion, this study will aim to evaluate the intervention effects of omega-3 PUFA-enriched eggs in patients with MetS, while systematically exploring the underlying mechanisms. The findings will provide valuable scientific evidence for related research and practical applications in community-based nutritional interventions for the elderly.

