### Study participants

2.4

Participants will be recruited from Guangyang District, Langfang City, Hebei Province, using purposive and convenience sampling methods. Recruitment strategies will include community health clinic screenings, health education sessions, and telephone invitations.

Inclusion Criteria: Community-dwelling adults aged ≥ 65 years with a clinical diagnosis of MetS will be included. MetS will be defined as meeting at least three of the following five criteria: (i) abdominal obesity: waist circumference ≥90 cm (men) or ≥85 cm (women); (ii) hyperglycemia: fasting plasma glucose ≥6.1 mmol/L or 2-h post-load glucose ≥7.8 mmol/L on oral glucose tolerance test (OGTT), or previously diagnosed diabetes currently under treatment; (iii) elevated blood pressure: systolic blood pressure ≥130 mmHg and/or diastolic blood pressure ≥85 mmHg, or previously diagnosed hypertension currently under treatment; (iv) hypertriglyceridemia: fasting triglycerides ≥1.70 mmol/L; and (v) low high-density lipoprotein cholesterol: fasting HDL-C < 1.04 mmol/L.

Exclusion criteria: (i) medical conditions—severe hepatic or renal impairment, immunodeficiency disorders, active infectious diseases, type 1 diabetes, malignant hypertension, malignancy, thyroid dysfunction, electrolyte disturbances, acute diabetic complications or severe chronic complications (including cardiovascular or cerebrovascular events within the preceding month), prior bariatric surgery, or recent significant weight change (>5% over 3 months or >10% over 6 months); (ii) dietary factors—adherence to specialized therapeutic diets or substantial dietary modification within 12 weeks prior to enrollment; (iii) cognitive and functional status—severe medical or psychiatric disorders, or cognitive, visual, or hearing impairments that would preclude study compliance; (iv) medication and supplement use—current use of omega-3 PUFA supplements or medications known to affect lipid metabolism (concomitant medication use will be systematically documented during the screening visit via a comprehensive medication questionnaire); and (v) allergies—documented egg allergy.

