Participants who require medical treatment, initiate lipid-lowering therapy, or experience acute illness or exacerbation of chronic conditions during the intervention period will have the onset time, duration, and treatment measures documented in detail. Dietary assessments and other measurements will be scheduled within prespecified time windows for each study phase to minimize potential confounding effects. The study flowchart is presented in Figure 1. The schedule for enrollment, intervention, follow-up, and assessment is shown in Table 2. The intervention components and responsible personnel for the study are summarized in Table 3.

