### Primary outcome

5.3

The primary outcome will be defined as the longitudinal trajectory of fasting triglycerides (TG) measured at Weeks 0, 4, 8, and 12. The primary statistical analysis will focus on the group × time interaction, indicating differences in TG trends over time among intervention groups. The pre-specified primary comparison will be between the omega-3 PUFA-enriched egg group and the standard egg group to evaluate intervention efficacy. Exploratory pairwise comparisons will also be conducted for other group combinations not specified in the primary hypothesis.

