## Data entry and analysis

7

**Data entry:** Questionnaire data will be collected directly via electronic forms with built-in logic checks to ensure the accuracy and completeness of data entry, minimizing errors in data recording.

**Statistical analysis:** Statistical analyses will be performed using SPSS 24.0 and R 4.2.0 software. For baseline variables, continuous variables will be analyzed using one-way analysis of variance (ANOVA) or kruskal-wallis tests, while categorical variables will be analyzed using chi-square tests or Fisher's exact tests.

For longitudinal outcome measures, mixed-model repeated measures analysis of variance (MMRM) with an unstructured covariance matrix will be adopted as the primary analytical method. This model will include intervention group, time point, and group × time interaction as fixed effects, with subject-specific random intercepts. Pre-specified covariates (including age, sex, body mass index (BMI), baseline dietary intake, physical activity, baseline clinical parameters, and compliance) will be adjusted in the primary analysis based on their correlation with outcomes and clinical relevance.

Missing data will be handled using intention-to-treat (ITT) analysis with mixed models, which can accommodate unbalanced data under the missing at random (MAR) assumption. Sensitivity analyses will include complete case analysis and multiple imputation by chained equations (MICE) to verify the robustness of the results.

For multi-omics analyses (microbiome and metabolomics), Benjamini-hochberg false discovery rate (FDR) correction (*q* < 0.05) will be applied to control the expected proportion of false positives among the results. Microbiome data will undergo centered log-ratio (CLR) transformation to address compositional data constraints. Non-parametric methods [Friedman test, permutation-based multivariate analysis of variance (MANOVA)] will be used when the assumptions of normality or homogeneity of variance are violated. Principal coordinate analysis (PCoA) based on bray-curtis distances will be used to analyze microbiome composition, and principal component analysis (PCA) will be applied to metabolomics data. Associations between the microbiome and metabolome will be analyzed using sparse partial least squares (sPLS) or canonical correlation analysis (CCA), with FDR correction applied to ensure the reliability of the results.

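### An unrestricted rule to drop the data of participants who cease to satisfy the study criteria contradicts the intention-to-treat analysis and could bias the primary triglyceride comparison

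*Protocol article*

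**What the plan says.** Three places in the protocol article bear on whose data enter the analysis.

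- **Section 8 (Discussion, data quality control):** "Data from participants who no longer meet the study criteria will be excluded, and the reasons for withdrawal will be documented in detail".
- **Section 7 (Data entry and analysis):** "Missing data will be handled using intention-to-treat (ITT) analysis with mixed models", under a missing-at-random (MAR) assumption. It adds: "Sensitivity analyses will include complete case analysis and multiple imputation by chained equations (MICE) to verify the robustness of the results".
- **Section 3.5 (Intervention initiation and follow-up data collection):** for "Participants who require medical treatment, initiate lipid-lowering therapy, or experience acute illness or exacerbation of chronic conditions during the intervention period", the onset, duration and treatment are to be recorded. Removal of their data is not mentioned.

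The primary outcome and the criteria are set out elsewhere.

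- **Section 5.3:** "The primary outcome will be defined as the longitudinal trajectory of fasting triglycerides (TG) measured at Weeks 0, 4, 8, and 12". The primary comparison is enriched eggs against regular eggs.
- **Section 2.4:** metabolic syndrome (MetS) requires at least three of five components, one of which is "iv) hypertriglyceridemia: fasting triglycerides ≥1.70 mmol/L". One exclusion is "current use of omega-3 PUFA supplements or medications known to affect lipid metabolism".

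**The concern.** A participant can only cease to meet a criterion after having met it, so the Section 8 sentence describes a change after entry. It carries no restriction to a secondary analysis set. An intention-to-treat analysis does not remove randomised participants for what happens to them later, so Sections 7 and 8 cannot both be followed. Section 3.5 points a third way by recording such events without excluding anyone. A data manager would have to choose among the three, possibly after TG results are visible.

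What is at stake is the primary comparison. Two of the study criteria are linked to TG: the TG component of MetS, and the bar on lipid-affecting medication. If the rule were applied to either, the chance of being excluded could depend on TG itself and could differ between the egg arms. Randomisation would then no longer protect the comparison.

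**Working it through.** **1. The plan's own sample size.** Inputs from Section 2.3: two-sided alpha 0.05 (z = 1.96), power 80% (z = 0.84), SD 58 mg/dL, difference 35 mg/dL, dropout 25%.

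- n = 2 × (1.96 + 0.84)² × 58² / 35² = 43.06, rounded up to 44 per group. This matches the plan.
- 44 / (1 − 0.25) = 58.7, rounded up to 59, then set at 60. This matches the plan.

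**2. Power if the rule removes more people.** With 60 × 0.75 = 45 evaluable per arm, power is 81.7%. The document gives no further exclusion rate, so a range is shown.

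| Further share removed (assumed) | Evaluable per arm | Power |
|---|---|---|
| 0% | 45 | 81.7% |
| 5% | 42.75 | 79.7% |
| 10% | 40.5 | 77.5% |
| 15% | 38.25 | 75.1% |
| 20% | 36 | 72.6% |

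The loss of power is modest. Bias is the larger issue.

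**3. Illustration of bias.** Taken from the document: mean TG 140.9 mg/dL, SD 58, difference 35, threshold 1.70 mmol/L (1.70 × 88.57 = 150.6 mg/dL). Everything else is assumed:

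- TG is lognormal, with a baseline-to-follow-up correlation of 0.5 or 0.7.
- There is no mean change on regular eggs; on enriched eggs, follow-up values are scaled so that the mean falls by 35.
- MetS status hinges on the TG component in 30% or 50% of participants.
- Half of those with follow-up TG of 200 mg/dL or more start lipid-lowering therapy.

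The quantity is the between-arm difference in mean change, with whole participants removed. It is a two-visit simplification, not the full repeated-measures model. Shares removed are given as regular / enriched.

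| Correlation; MetS hinges on TG | All kept | (a) Drop if MetS status lost | (b) Drop if lipid drug started | (a) and (b) |
|---|---|---|---|---|
| 0.5; 30% | −35.1 | −34.0 (4.6% / 7.9%) | −31.7 (7.0% / 1.8%) | −30.6 (11.6% / 9.7%) |
| 0.5; 50% | −34.9 | −32.7 (7.7% / 13.1%) | −31.6 (7.0% / 1.8%) | −29.5 (14.7% / 14.9%) |
| 0.7; 30% | −35.0 | −33.9 (3.5% / 7.2%) | −32.7 (7.0% / 1.8%) | −31.5 (10.5% / 9.0%) |
| 0.7; 50% | −35.0 | −32.9 (5.9% / 12.1%) | −32.6 (7.0% / 1.8%) | −30.6 (12.9% / 13.8%) |

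With both routes the shrinkage is 35 − 31.5 = 3.5 to 35 − 29.5 = 5.5 mg/dL, which is 3.5/35 = 10% to 5.5/35 = 16%. In the second row the arms lose almost equal shares, yet the shrinkage is greatest: route (a) removes mainly enriched-egg participants with falling TG, and route (b) mainly regular-egg participants with high TG. Similar exclusion counts would therefore not be reassuring.

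**4. Can the planned methods repair it?**

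- *Whole record deleted:* the observed TG values that would explain the exclusion leave the model as well, so a mixed model under MAR cannot use them. Complete-case analysis and MICE do not restore the deleted data.
- *Only values after the event deleted:* if the event was triggered by a TG value that stays in the model, the gap can be MAR and the mixed model can handle it.

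Section 8 does not say which applies.

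**The case against.** The sentence names no criterion, and no section describes re-checking eligibility after randomisation; Section 3.1 settles final eligibility at enrolment. It stands in a paragraph on data quality and speaks of withdrawal, so it may have been meant for participants who withdraw or were enrolled in error. Improving metabolic indicators is the trial's aim, so a deliberate rule to discard people who recover from MetS would be odd. Section 3.5 suggests that data after the start of lipid-lowering therapy are kept. All of this stands as a reading of intent, but none of it is written as a limit on the rule.

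A reader might infer several stronger things that the documents do not support:

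- **That people will be removed because of their TG.** This is a possible consequence of the criteria, not something the protocol states.
- **That any acute illness triggers exclusion.** Section 2.4 lists specific conditions, such as active infection and acute diabetic complications. The general phrase belongs to the Section 3.5 recording list.
- **That the protocol expects non-random missing data in the primary comparison.** The remark that "the potentially higher attrition rate in the blank control group could cause non-random missing data" concerns the blank control arm, which is outside that comparison.
- **That the bias is large and known.** If the highest-TG 10% of the regular arm and 5% of the enriched arm were cut off, a truncated normal with SD 58 would shift the means by 11.3 and 6.3 mg/dL, a bias of 5.0 (14% of 35). With 15% against 5% it would be 15.9 − 6.3 = 9.6 (27%). These shares have no source, and the model leaves out loss of MetS status altogether.
- **That complete-case analysis must give way to tipping-point or reference-based imputation.** That is a preference, and commonly a matter for the analysis plan, which is not shown.

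**Conclusion.** The rule is wrong as written. It is unrestricted exclusion after randomisation, it contradicts the intention-to-treat analysis in Section 7, and it does not agree with Section 3.5. This conclusion rests on the text alone and needs no numerical assumption.

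That the exclusion could bias the enriched-versus-regular comparison follows from the overlap between the criteria and the outcome, provided that those criteria are applied after randomisation. The mixed model's failure to repair it holds if whole records are deleted. The document gives neither the criteria to be re-checked nor the number affected, so size and direction are unknown. The 3.5 to 5.5 mg/dL shrinkage is an illustration under the assumptions above. The direction could reverse, for instance if participants whose TG fell were removed more often from the regular-egg arm.

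**What to change.** Reconcile Sections 3.5, 7 and 8. Replace the Section 8 sentence with wording such as:

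*All randomised participants are analysed in their assigned arm, using all TG values collected. Exclusions based on the study criteria are made only in a per-protocol sensitivity analysis, labelled as such, with the criteria and the numbers excluded reported by arm.*

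Section 3.5 should then say that TG values collected after the start of lipid-lowering therapy stay in the primary analysis. This concerns only which data are analysed; no rule on treatment or withdrawal is proposed.

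The cost is a change of wording and one labelled sensitivity analysis. The primary estimate may be slightly diluted by on-study lipid-lowering therapy. Table 1 records that recruitment has not begun, so the change can be made before any outcome data exist.
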